## Abstract

**Background:**

More than 100 surgical approaches to treat rectal prolapse have been described. These can be done through the perineum or transabdominally. Delorme’s procedure is the most frequently used perineal, resection rectopexy the most commonly used abdominal procedure. Recurrences seem more common after perineal compared to abdominal techniques, but the latter may carry a higher risk of peri- and postoperative morbidity and mortality.

**Methods/Design:**

DeloRes is a randomized, controlled, observer-blinded multicenter trial with two parallel groups. Patients with a full-thickness rectal prolapse (third degree prolapse), considered eligible for both operative methods are included. The primary outcome is time to recurrence of full-thickness rectal prolapse during the 24 months following primary surgery. Secondary endpoints are time to and incidence of recurrence of full-thickness rectal prolapse during the 5-year follow-up, duration of surgery, morbidity, hospital stay, quality of life, constipation, and fecal incontinence. A meta-analysis was done on the basis of the available data on recurrence rates from 17 publications comprising 1,140 patients. Based on the results of a meta-analysis it is assumed that the recurrence rate after 2 years is 20% for Delorme’s procedure and 5% for resection rectopexy. Considering a rate of lost to follow-up without recurrence of 30% a total of 130 patients (2 x 65 patients) was calculated as an adequate sample size to assure a power of 80% for the confirmatory analysis.

**Discussion:**

The DeloRes Trial will clarify which procedure results in a smaller recurrence rate but also give information on how morbidity and functional results compare.

**Trial registration:**

German Clinical Trial Number DRKS00000482

## Background

Full-thickness prolapse of the rectum is defined as protrusion of the full thickness of the rectal wall through the anus. There is a peak in the incidence of this disease in the seventh decade of life. A total of 80% to 95% of the patients are women
[1,2]. The etiology of rectal prolapse is still unknown. Fifty percent to seventy percent of patients complain of longstanding constipation, the rate of fecal incontinence ranges between 40% and 80%
[3-6]. Other predisposing conditions include chronic straining defecation, pregnancy, previous surgery, and neurological disease. There is probably a genetic disposition to this condition.

Treatment of rectal prolapse is usually surgical. More than 100 surgical approaches have been described in the literature. The aims of the operation are to correct the rectal prolapse, to restore normal bowel function, and to avoid a recurrence of full-thickness rectal prolapse. For many patients, constipation and fecal incontinence improve after surgery
[4,7,8].

Basically, two different surgical approaches can be distinguished: perineal and transabdominal procedures. In general, perineal surgical repairs supposedly cause less morbidity and mortality compared with abdominal operations
[7,9,10]. They are considered especially indicated in the elderly and/or high-risk patients as they can also be done in spinal or epidural anesthesia
[9,11,12]. On the other hand, recurrences seem more frequent after perineal techniques than after abdominal operations
[1-3,13]. Abdominal repairs involve fixing the rectum to the sacrum by using either mesh or sutures. In addition to rectopexy a sigmoid resection is commonly performed. Laparoscopic repair of rectal prolapse has similar morbidity and recurrence rates as open surgery
[7,14]. There are data suggesting that the laparoscopic compared to the conventional approach has short-term benefits as described for other laparoscopic abdominal procedures (reduced length of hospital stay, less postoperative pain, faster return to normal bowel function, and less wound complications)
[9,15]. But when using a modern fast-track regime (involving multimodal balanced anesthesia and analgesia including peridural catheter, early normal nutrition and mobilization as well as avoidance of tubes and catheters) the advantages of a laparoscopic approach have become somewhat less clear
[15-17]. In general the fast-track regime allows enhanced recovery and discharge of patients compared to conventional postoperative management. Application of such a fast-track regime allows compensation of assumed disadvantages like more pain or slower mobilization of patients after open abdominal surgery compared to laparoscopic surgery.

In conclusion, perineal as well as abdominal (mostly laparoscopic) procedures remain the established options in the surgical treatment of rectal prolapse without evidence from adequately designed randomized studies which of these procedures are superior. There are only insufficient data available on the long-term benefits and risks, quality of life, and total treatment costs. Our trial aims to contribute to the very scarce high-level-evidence basis of randomized trials comparing a perineal *vs*. an abdominal approach. The urgent need for a randomized trial such as DeloRes was also pointed out in the Cochrane Review by Tou in 2009
[18].

## Methods/Design

### Trial design

DeloRes is a randomized, controlled, observer-blinded multicenter trial with two parallel groups.

### Patient population

#### Inclusion criteria

• Full-thickness rectal prolapse, externally visible on straining

• ASA-Score I-III

• Patient is suited for both standardized surgical approaches

• Patient is able to cooperate

 · Patient has given written informed consent

• Aged 18 years or older

#### Exclusion criteria

• Recurrence of full-thickness rectal prolapse

• Patient with stoma

• Patient with inflammatory bowel disease

• Pregnancy or breastfeeding

• Patient currently under chemotherapy

• Active malignant disease and life expectancy less than 24 months

• Body mass index greater than 40

• Participation in another intervention trial with interference of intervention and outcome of this study

The aim was to exclude as few patients as possible, but nevertheless minimize attrition bias in long-term follow-up and enable a high recruitment rate given the fact that patients presenting with full rectal prolapse are a small population of a reasonably higher population of patients not willing to present at their physicians because of misinformation or shame.

Thus patients with recurrent rectal prolapse would often not be acceptable for surgeons to be randomized to perineal vs. abdominal approach especially if the prior surgery had been a perineal approach. Patients not surviving at least 24 months would not be available for the primary endpoint visit at 24 months postoperatively. And patients with BMI > 40 had been excluded as they are very few and do not represent the common patient habitus of rectal prolapse.

### Scheme of intervention

DeloRes will be performed in 13 trial centers. All participating centers are cooperating units with a special focus on colorectal surgery and all centers perform between eight and sixty surgical interventions for rectal prolapse per year. In order to minimize performance bias, only surgeons with an adequate experience in performing the approaches investigated operate on patients in this study (minimum number of procedures performed (‘life-time experience’): Delorme’s procedure=20, (laparoscopic) resection rectopexy=20). Each study center provides at least one surgeon with the required experience for Delorme’s procedure and one surgeon with the required experience for (laparoscopic) resection rectopexy (expertise based, best team approach). To ensure standardization for all participating centers an operative manual with standardized video sequences will be prepared. Moreover, consented crucial steps of each procedure will be captured in the clinical record file. In addition, in order to allow confirmation of a certain procedure quality, selected digital photos will be taken.

To reflect current practice and to increase external validity of the trial, perioperative standards (for example, bowel preparation, parenteral nutrition, fast-track, postoperative application of laxatives) will not be strictly standardized. Each trial center, however, will document its own standards in a short questionnaire and agrees not to change this standard during trial recruitment.

### Recruitment and trial timeline

Recruitment of participants started in September 2010. The duration of the trial for each patient is expected to be 60 months with follow-up at 6, 12, 24, and 60 months after the primary surgery.

### Treatment assignment and randomization

Consecutively screened and eligible patients will be included in the trial. In order to achieve comparable intervention groups, patients will be allocated by preoperative randomization 24 to 48 h prior to surgery after given written informed consent using a centralized web based tool (
http://www.randomizer.at). Block randomization stratified by center will be applied to achieve equal group sizes per center.

### Interventions and trial flow

The laparoscopic approach is considered the standard approach for the transabdominal operation of full-thickness rectal prolapse. Laparoscopic resection rectopexy is suggested to yield better results in the early postoperative phase in comparison to the open approaches with equal recurrence rates in comparison to the open approach. However, the advantages of a laparoscopic approach become somewhat less evident under a fast-track regime, therefore open resection rectopexy is also acceptable via a Pfannenstiel incision. The latter approach has proven to be only moderately invasive in numerous procedures of the lower abdomen. The most frequently used perineal procedure is Delorme’s procedure, which shows low postoperative morbidity. The trial flow is illustrated in Figure
1.

**Figure 1 F1:**
[figure not shown]
Trial flow/intervention scheme.

#### Description of trial days

All patients will be informed about the purpose of the trial and surgical treatment modalities comprising their benefits as well as risks. The schedule of trial interventions is presented in Table 
1.

**Table 1 T1:** Study visits of DeloRes

	**Visit 1**	**Visit 2**	**Visit 3**	**Visit 4**	**Visit 5**	**Visit 6**	**Visit 7**
	**Screening**	**Surgery**	**Day of Discharge**	**6 months after Surgery**	**12 months after Surgery**	**24 months after Surgery**	**60 months after Surgery**
Demographic and clinical baseline data	×						
Inclusion/Exclusion	×						
Randomization	×						
Intervention		×					
Assessment of Complications and Safety		×	×	×	×	×	×
Recurrence				×^a^	×^a^	×	×
Secondary endpoints		×	×	×^a^	×^a^	×	
SF-12	×			×^a^	×^a^	×	
Herold constipation score	×			×^a^	×^a^	×	
Wexner score	×			×^a^	×^a^	×	
Rockwood-FIQLScore	×			×^a^	×^a^	×	

^a^It is intended that patients come to the trial sites for all follow-up visits. If they are unable to travel they will be visited by a study nurse. At the 6- and 12-month follow-up visits, recurrence status, secondary endpoints can exceptionally be assessed by phone interview and/or by mailing questionnaires.

### Outcome measures and definitions

The clinically most relevant parameter in the treatment of full-thickness rectal prolapse is the time to recurrence. Therefore this parameter is defined as primary outcome measure, evaluated during the 24 months following primary surgery. Recurrence is defined as the circular protrusion of rectal mucosa through the anal canal and will be examined by standardized history, clinical examination, and photo documentation. To assess the primary outcome, patients are asked to perform a straining maneuver in a sitting position (patients not able to sit will be assessed in a lateral decubitus position). Then a photograph is taken during straining. The primary outcome is finally determined by the independent review board on the basis of the photograph.

Secondary endpoints are time to and incidence of recurrence of full-thickness rectal prolapse during 5-year follow-up, duration of surgical intervention, morbidity, SAE, all causes of mortality within 3 months after primary surgery (this period was chosen to get any mortality possible related to surgery. Patients with rectal prolapse are usually rather old and frail. There are multiple reasons for further morbidity or mortality which are expected to be unrelated to the surgical procedure in case they occur beyond the first 3 months), length of initial hospital stay, reoperation rate for recurrent prolapse, cumulative hospital stay and change in quality of life, constipation, and fecal incontinence as measured by appropriate questionnaires.

The time to and the incidence of recurrence of full-thickness rectal prolapse during a 5-year follow-up after primary surgery will be assessed as explained above. Morbidity occurring during the primary hospital stay is further differentiated into surgical and non-surgical complications, which are specifically defined as following: severity grading is done with the Clavien classification
[19] and for anastomotic leakage with the classification of the International Study Group of Rectal Cancer
[20]. The definitions of the secondary outcomes are shown in Table 
2. 

**Table 2 T2:** Definitions of secondary outcomes

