***Surgical complications***	
Postoperative ileus	Obstructive or paralytic symptoms after surgery with the need to suspend food intake and/or insert a gastric tube; this has to be confirmed radiologically (by abdominal sonography or plain abdominal X-ray or CT scan)
Postoperative hemorrhage	Need for administration of two or more red cell concentrates within the first 24 h postoperatively or need for reoperation
Surgical site infection	CDC definition [21]
Intra-abdominal abscess	Intra-abdominal collection of purulent or infected fluid (confirmed by culture) confirmed by puncture or by surgical reintervention
Anastomotic leakage	Grade A-C, Definition of grade according to International Study Group of Rectal Cancer 2010, diagnosed by CT scan with radiographic enema, endoscopy, drain secretion (stool) or reoperation

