***Non-surgical complications***	
Thrombosis	Clinical evidence (for example, pain, swelling, warmth, erythema) of a leg or pelvic vein thrombosis confirmed by duplex sonography or CT angiography, which was not previously known
Pulmonary embolism	Clinical (for example, tachycardia, dyspnea) and/or radiological evidence of pulmonary embolism confirmed by spiral CT or lung perfusion scintigram
Postoperative pulmonary infection	At least three of the following:
	- temperature > 38°C
	- purulent tracheal secretion
	- leucocytes >12 or < 4.5 [10E9/L]
	- elevated CRP
	AND Evidence for pulmonary infection radiologically
Renal failure	Need for dialysis or hemofiltration
Cerebral insult	Ischemic or non-ischemic cerebrovascular event with persistent paresis or paralysis without previous history confirmed by CT or MRT
Myocardial infarction	Electrocardiogram (NSTEMI or STEMI) and enzyme (Troponin I) changes suggestive of myocardial infarction or needing admission to coronary care unit
*Serious adverse events*	SAE occurring from the day of randomization until regular end of trial follow-up or withdrawal
*Mortality*	All causes of mortality within 3 months after primary surgery
*Duration of surgical intervention*	First incision to the completion of skin closure (resection rectopexy) or the last coloanal suture (Delorme’s procedure)
*Length of initial hospital stay*	Means the hospitalization period from the primary operation date until the day of discharge (= postoperative hospital stay)
*Reoperation rate for recurrent prolapse*	Any surgical intervention for a recurrence
*Cumulative hospital stay*	Defined by the days in hospital after the primary surgery as well as the following hospitalizations due to complications or recurrence within 24 months after the primary operation
*Change of quality of life, constipation and incontinence*	
	Measured by means of the appropriate questionnaires SF-12, ( [22], validated in German), Herold constipation score ( [23], evaluated in German, but not yet published), Wexner-Score ( [10], non-validated in German, most commonly used score) and Rockwood-FIQLScore ( [24], validated), prior to the surgical intervention as well as 6, 12, and 24 months after the intervention

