### Safety assessments and reporting of adverse events

Analysis of safety-related data is performed with respect to frequency of serious adverse events, frequency of serious adverse events stratified by intensity and causality, and frequency of morbidity in both treatment groups.

From the day of randomization until the regular end of trial follow-up or until premature withdrawal of the patient, all serious adverse events must be documented on a ‘serious adverse event form’ available in the investigator site file.

A serious adverse event will be defined as an event that results in death, is immediately life-threatening, requires or prolongs hospitalization beyond the 20th postoperative day for any medical reason, requires readmission for any medical reason within 3 months after the operation within this trial, requires readmission for treatment of surgical complications related to the study operation beyond 3 months postoperatively, or results in persistent or significant disability or incapacity. Serious adverse events will be classified in intensity (mild, moderate, severe), outcome (recovered completely, recovered with sequelae, not recovered, death, unknown), and causality (unrelated, possibly related, probably related, definitely related, not assessable).

The assessment is based on surgical findings and the clinical course of the patient. It needs to be done by the investigators. Serious adverse events have to be reported by the attending physician to the coordinating investigator or one of both study supervisors within 24 h after the SAE becomes known.

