#### Analysis

The allocation of all patients to the different analysis populations will be defined prior to the analysis (full analysis set (FAS) according to the intention-to-treat principle (ITT; all randomized patients as randomized), per protocol (PP) analysis set, safety analysis set). The procedure of allocation will be documented in the statistical analysis plan. During the data review, deviations from the protocol will be assessed as ‘minor’ or ‘major’. Major deviations from the protocol will lead to the exclusion of a patient from the PP analysis set.

The confirmatory analysis is performed for the full analysis set. The null-hypothesis ‘no difference in the time to recurrence of full-thickness rectal prolapse between experimental and control intervention during the 2-year follow-up after randomization’ is tested by application of the log rank test stratified by center at the two-sided level α=5%. Drop-out and lost-to-follow-up without recurrence of full-thickness rectal prolapse are considered as censoring events.

For the analysis of the secondary outcomes descriptive methods will be used, including the calculation of appropriate summary methods for the empirical distribution as well as calculation of descriptive two-sided *P* values for comparisons of treatment groups. A special focus of the exploratory analyses will be on the time course of the primary as well as the secondary endpoints. Additionally, sensitivity analyses will be conducted for different study populations (per protocol population, appropriate subgroups). Further exploratory analyses will be performed to identify potential prognostic factors for the intervention effect. The time to recurrence of full-thickness rectal prolapse will additionally be analyzed applying a Cox regression model that includes covariates of potential prognostic value.

The safety analysis is based on all randomized patients who were treated with the interventions under investigation. The analysis includes calculation and comparison of the rates of specified complications (see secondary endpoints) and serious adverse events as well as of severity and relationship to intervention and graphical display of the time course. Furthermore, statistical methods are used to assess the quality of data and the homogeneity of intervention groups.

All analyses will be done using SAS version 9.1 or higher.

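### Classified and graded morbidity is tied to a window that ends at discharge, so observation time may differ between arms and the complication comparison can be biased

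*Protocol article*

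**What the plan says.** All references are to the protocol article.

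- **Outcome measures and definitions.** Morbidity appears among the secondary endpoints without a window. The text then specifies: "Morbidity occurring during the primary hospital stay is further differentiated into surgical and non-surgical complications". The Clavien grading and the separate grading of anastomotic leakage follow in that sentence.
- **Table 2, length of initial hospital stay.** "Means the hospitalization period from the primary operation date until the day of discharge (= postoperative hospital stay". The end of the morbidity window is thus the end of a period whose length is itself a secondary outcome.
- **Table 2, other windows.** Mortality has a fixed window: "All causes of mortality within 3 months after primary surgery". SAEs have a long one: "SAE occurring from the day of randomization until regular end of trial follow-up or withdrawal". One complication has a time limit on one of its criteria: "Need for administration of two or more red cell concentrates within the first 24 h postoperatively or need for reoperation".
- **Table 1.** The row "Assessment of Complications and Safety" is marked from surgery and discharge through 6, 12, 24 and 60 months.
- **Safety assessments.** An event is serious if, among other criteria, it "requires readmission for any medical reason within 3 months after the operation within this trial".
- **Analysis.** The safety analysis includes "calculation and comparison of the rates of specified complications (see secondary endpoints". No allowance for unequal observation time is stated. Secondary outcomes are analysed descriptively.
- **Discussion.** The authors say that fewer recurrences after the abdominal operation might be outweighed by considerably higher morbidity.

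**The concern.** Length of stay is determined after randomization. It can depend on the operation, and a complication can itself delay discharge. If complications are classified and graded only up to discharge, a patient who stays longer is observed longer. A wound infection arising on day 8 would be classified for a patient still in hospital but not for one discharged on day 4. The two arms could then show different rates although their risk over any common period is equal.

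The article gives reasons to expect that stays could differ. The Background lists a shorter stay as a benefit of laparoscopic over conventional surgery and says that fast-track care allows earlier discharge. The abdominal arm may be operated laparoscopically or open, and fast-track practice is left to each centre. The Discussion describes perineal approaches as less invasive.

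At stake is the morbidity side of the trade-off that the authors set against recurrence. The same section justifies 3 months for mortality on the ground that later morbidity or mortality is expected to be unrelated to surgery. That reasoning fits morbidity too, yet only mortality receives the fixed window.

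**Working it through.** **No figure to reproduce.** The plan attaches no number to this rule. The check is a comparison of the stated windows, followed by an illustration.

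**Windows side by side**

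| Outcome | Window | Same length in both arms? |
|---|---|---|
| Classified and graded morbidity | Operation to discharge | Only if stays are equal |
| Mortality | 3 months from surgery | Yes |
| SAE | Randomization to end of follow-up or withdrawal | Same rule |
| Readmission for any medical reason, as an SAE | 3 months from surgery | Yes |
| Complication assessment, Table 1 | Every visit to 60 months | Same schedule |

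Only the first window has a length that treatment can change directly.

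**What SAE reporting leaves open.** After discharge, an event must be fatal, life-threatening, lead to a qualifying hospitalization or readmission, or cause lasting disability to be an SAE. A wound infection or leg thrombosis managed without readmission can meet a Table 2 definition and still not be an SAE. SAEs are rated mild, moderate or severe, not by the Clavien classification.

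**Illustration.** Assumptions, none from the article: the same true 30-day complication risk R in both arms; onset exponential with mean m days, truncated at 30 days; a fixed stay L in each arm.

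Counted risk = R × (1 − exp(−L/m)) / (1 − exp(−30/m))

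Apparent risk ratio, longer (b) to shorter (a) stay = (1 − exp(−b/m)) / (1 − exp(−a/m)). R cancels.

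| Stays (days) | m = 5 | m = 8 | m = 12 |
|---|---|---|---|
| 4 vs 5 | 1.15 | 1.18 | 1.20 |
| 4 vs 7 | 1.37 | 1.48 | 1.56 |
| 5 vs 8 | 1.26 | 1.36 | 1.43 |
| 5 vs 10 | 1.37 | 1.54 | 1.66 |

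Worked example: R = 30%, m = 8, stays of 5 vs 8 days. Counted risks are 14.3% and 19.4%, a ratio of 1.36 and a difference of 5.1 percentage points.

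For R = 20% or 30%, the differences over this grid run from 1.2 to 7.6 percentage points. With 65 patients per arm (from the sample size section) and a normal approximation for two proportions, the chance of a nominal two-sided p < 0.05 against the longer-stay arm is about 5% to 22%. It would be 2.5% in that direction without the artefact.

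A further scenario uses R = 20%, stays of 4 vs 9 days and median onset of 3, 5 or 7 days, with counted risk = 0.20 × (1 − 0.5^(L/median)) / (1 − 0.5^(30/median)):

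| Median onset (days) | 4-day stay | 9-day stay | Ratio |
|---|---|---|---|
| 3 | 12.1% | 17.5% | 1.45 |
| 5 | 8.6% | 14.5% | 1.67 |
| 7 | 6.9% | 12.4% | 1.80 |

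Together, the ratio runs from 1.15 to 1.80 for stays differing by 1 to 5 days.

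**After the fix.** With one fixed window from surgery, the ratio is 1.00 and the difference 0, whatever the stays. With equal stays, the in-hospital window also gives 1.00.

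**The case against.** The strongest reply is that the article does not ignore complications after discharge. The endpoint list names morbidity without a window, the Table 2 complication definitions carry no general in-hospital limit, and the safety analysis mentions a display of the time course. Table 1 assesses complications at every later visit. Serious events, including any medical readmission within 3 months, are captured under the same rule in both arms, and cumulative hospital stay counts rehospitalization for complications to 24 months. A reader might infer that morbidity is counted only in hospital; these passages do not support that. What stands is narrower: the sentence on classification and grading names the primary stay, and nothing in the article extends it.

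A reader might also infer that the stay is known to differ by operation. No passage gives a stay for either procedure or says that they differ; the trial is to measure it. The Background even says that fast-track care compensates for assumed disadvantages of open abdominal surgery. Unstandardised centre practice does not by itself separate the arms, because randomization is stratified by centre and each centre agrees to keep its standard. Stratification does not, however, remove a difference in stay that the operation itself causes.

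Two further points stand. Early events, such as haemorrhage under its 24-hour transfusion criterion, are hardly affected. Surgical site infection follows a cited definition that is not shown and may carry its own window. The full protocol is not shown either and may state the morbidity window more fully; the sentence published here should then agree with it.

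**Conclusion.** The point holds in limited form. The stated window for classified and graded morbidity ends at an event that treatment and the complications themselves can influence, and the rates are compared with no stated allowance for this. The comparison can be biased against whichever arm stays longer. To say that it is biased would go further than the article allows, because the stays and onset times are unknown.

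The gap is mainly non-serious complications after discharge and the classification and grading of later ones. An apparent risk ratio of roughly 1.15 to 1.8 rests wholly on assumed onset times and on stays assumed to differ by 1 to 5 days; its upper end needs a gap of five days and late onset. The illustration holds the stay fixed, so it leaves out any prolongation of stay by a complication.

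The comparison is secondary and descriptive, and the confirmatory log rank test on recurrence is untouched. It still deserves correction, because the Discussion weighs morbidity against the primary result.

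**What to change.** Define the classified and graded morbidity endpoint over one fixed window from surgery, the same in both arms. Either 30 days or the 3 months already used for mortality and readmission SAEs would serve. Apply the Table 2 definitions, the surgical/non-surgical split and the Clavien and leakage grading to every complication with onset in that window, using the data from the discharge and 6-month visits. Report in-hospital morbidity as a descriptive supplement.

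The cost is an amendment to one definition and an onset date for each complication. The case report form is not shown, so that field may already exist. No extra visit is needed. The small downside is that some non-serious events after discharge rely on recall at 6 months, in both arms.
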